# Self-Management Strategies for Low Back Pain Among Horticulture Workers: Protocol for a Type II Hybrid Effectiveness-Implementation Study

**DOI:** 10.2196/64817

**Published:** 2025-01-28

**Keywords:** low back pain, self-management, implementation, horticulture workers, video training, video feedback, text message reminders, agriculture, ergonomic, nonpharmacological

## Abstract

**Background:**

Low back pain (LBP) is highly prevalent and disabling, especially in agriculture sectors. However, there is a gap in LBP prevention and intervention studies in these physically demanding occupations, and to date, no studies have focused on horticulture workers. Given the challenges of implementing interventions for those working in small businesses, self-management offers an attractive and feasible option to address work-related risk factors and manage LBP.

**Objective:**

This study will (1) investigate the effectiveness of self-management strategies for nursery and landscape workers by comparing within-subject control and intervention periods and (2) determine if adoption and effectiveness differs between participants randomly assigned to review self-management videos only and those who also receive multimodal implementation support. We will also identify contextual factors impacting effectiveness and implementation.

**Methods:**

A pragmatic, mixed methods, hybrid effectiveness and implementation design will be used to compare back pain with work tasks, disability, medication and substance use, and psychological factors between a baseline control and intervention periods. We aim to recruit 122 English- and Spanish-speaking horticulture workers with back pain, 30 supervisors, and 12 focus group participants. Participants will review short video modules designed to increase awareness of opioid risk and introduce self-management and ergonomic choices and use 1 self-management and 1 ergonomic strategy for 10 weeks. They will be randomly assigned to 2 implementation groups: video modules only or video + multimodal personalized support (checklist guidance, review of video feedback for ergonomic problem-solving, and text message reminders). Questionnaires will be administered at 3-month time points: baseline, pre- and postintervention, and at 3 and 6 months. Qualitative analysis of field notes, open-ended comments, and focus groups will expand understanding of results with comprehensive documentation of the context, barriers and facilitators, and reasons for adoption.

**Results:**

The project was funded on September 29, 2023 (Centers for Disease Control and Prevention National Institute of Occupational Health and Safety, CDC NIOSH; U54OH011230-07S1), as a core research grant for the Southeast Coastal Center for Agricultural Health and Safety. The design, creation, and editing of English and Spanish videos was completed in June 2024 after comprehensive formative evaluation. Enrollment began in June 2024 with anticipated completion in 2027.

**Conclusions:**

We hypothesize that both self-management interventions will result in reductions in work task pain and disability and that the video enhanced with multimodal personalized support will result in greater reductions than the video alone. If self-management is effective, mitigating pain positively impacts quality of life, productivity, and retention, while increasing the use of nonpharmacological alternatives to opioids addresses an important public health issue. Implementation aims will help inform reasons for results, barriers and facilitators, and potential for similar interventions in these and similar industries with physically challenging outdoor work.

**Trial Registration:**

ClinicalTrials.gov NCT06153199; http://clinicaltrials.gov/study/NCT06153199

**International Registered Report Identifier (IRRID):**

DERR1-10.2196/64817

## Introduction

### Background

Low back pain (LBP) is the most common musculoskeletal disorder among agricultural and horticultural workers [1-5], negatively impacting worker’s physical and mental health, increasing absenteeism, and shortening work longevity [6-11]. Further, LBP contributes to lower productivity, loss of experienced workers, and increased workman’s compensation costs. The financial impact of high out-of-pocket costs and lack of paid leave often drive agricultural and horticulture workers to seek pain relief from prescription medications and illicit substances [12-14]. In one study of farmers with LBP, 71% relied on pain medication without consulting a physician compared to only 35% of white-collar workers [15].

Viable alternatives to pharmacological management of LBP have never been more important [16,17]. Despite guidelines recommending nonpharmacologic management, opioids are commonly prescribed for work-related injury and pain more frequently than for nonoccupational musculoskeletal disorders [18-22]. Although opioid prescribing has declined gradually since 2010, opioid fatalities from prescription and illicit synthetic opioids have continued to rise [20,23]. The precipitous increase in opioid overdose associated with fentanyl manufactured in clandestine laboratories [23,24] has elevated the importance of highlighting and promoting uptake of nonpharmacological alternatives for management of LBP [20]. In rural areas, opioid prescription rates are particularly high [25], and access to nonpharmacologic treatment options is limited [16]. A preliminary study supporting this protocol found that over half of agricultural workers (n=129) reported using opioids at some point [14]. Of those who had used opioids, most (77%) reported they received a prescription for a work-related injury. Participants explicitly linked work hazards and chronic pain with increased risk of opioid dependence, citing the need to continue working and “live with pain” as a cultural norm contributing to the problem [14]. While progression to opioid use disorder is complex, opioid misuse has devastating effects on health and work. A systematic review of the impact of prescription medications for occupational musculoskeletal injuries found that opioid use was associated with slower return to work, longer duration of disability, poorer self-reported work function, and poorer functional improvements [26]. Opioid prescriptions within the first 2 weeks of a work-related injury, opioid use for longer than 7 days, and higher dose supplies are associated with subsequent work disability or delayed recovery and greater work loss [26]. Owners of nursery and landscaping businesses in Florida reported problems with turnover, frequent absences, and low productivity among workers who used opioids, resulting in decreased labor availability [14]. Landscape and nursery work characteristics including low skill discretion, job strain (low control and high demand), high physical effort, and heavy lifting are risk factors for opioid use disorder [27]. Few opioid prevention efforts have been focused on underlying work-related factors such as musculoskeletal pain [18,28]. The substantial worker and employer burden of LBP in the horticulture industry and the devastating effects of opioid dependency highlight the need for efforts to manage and limit LBP and reduce unwarranted opioid use for musculoskeletal injury. Strategies to (1) increase workers’ awareness of the risks and consequences of opioid use, (2) encourage workers to discuss options with health care providers after more acute injuries, and (3) provide alternatives for nonpharmacological strategies to manage pain or limit ergonomic stress [28] may increase knowledge and self-efficacy while reducing stigma [20,28].

Self-management is defined as the ability to manage pain, treatment, psychosocial, and lifestyle implications of a chronic condition [29,30], with the overall goal for individuals to safely manage symptoms and lifestyle without seeking unnecessary medical intervention [30-33]. Encouraging active involvement and empowering individuals to select options to manage work-related pain tailored to each worker’s circumstances and preferences encompasses the principles of self-management for chronic conditions [6]. Effective self-management strategies should optimize pain coping strategies to manage and reduce symptom exacerbation through problem-solving [30]. Self-management is recommended for the management of chronic LBP in a number of guidelines and strategic initiatives [16,34,35], with moderate effectiveness for pain, and small to moderate effectiveness for pain-related disability reported in a systematic review and meta-analysis [36]. Increasing self-management of chronic pain that frequently limits work activities is one of the Health People 2030’s targets [35]. However, most studies investigating effectiveness of self-management approaches have involved patients receiving clinical care rather than groups who continue to work in physically demanding occupations. Self-management skills such as problem-solving, action planning, self-tailoring, and self-monitoring may provide a worker-centered approach for horticulture workers to promote self-efficacy and coping skills for adjusting work activities and managing pain [29,30,37].

There are limited training initiatives to address musculoskeletal pain for horticulture workers and most workers rely on supervisor’s advice or learning by experience. Many studies have concluded that education can positively influence work-related musculoskeletal pain by promoting behavioral change, modifying health beliefs, and improving attitudes, although gaps in optimal implementation persist [38]. Although some studies reported additive effects of improving physical activity or ergonomic adjustments [38], none focused on agriculture, nursery, or landscape workers. Collectively, there is a crucial need to determine optimal implementation of effective self-management programs for workers, especially for those who do not have resources to receive treatment in typical health care settings [39,40]. Therefore, examining the effectiveness of training to assist workers with learning self-management and ergonomic strategies will provide valuable information, while studying implementation outcomes will help determine engagement, adoption, and feasibility.

### Prior Work

This protocol builds from a preliminary study of streamlined individualized participatory ergonomic (PE) methods in clam aquaculture workers with similar physically challenging work [39,41]. Workers with chronic LBP were introduced to ergonomic concepts to reduce risk, selected 3 pertinent and acceptable strategies from a list, reviewed videos, and received text reminders. Significant improvements in disability, work-task pain, pain anxiety, and coping compared to baseline were observed (*P*<.05; n=19), with pain improvements greater than published minimal detectable change for 74% of the participants. The methods were both feasible and acceptable. These promising results led to recommendations to establish whether these approaches are effective in a larger cohort over longer timeframes, in different contexts, and with follow up [39].

We will investigate the effectiveness of self-management and ergonomic individual choices along with behavior change support for nursery and landscape workers. The first aim is to determine if self-management videos combined with multimodal personalized support is more effective than self-management videos alone for improving LBP management among horticulture workers. We hypothesize that compared to the video modules alone, the combined multimodal personalized support will result in (1) greater reductions in work task pain and disability, (2) lower prevalence of high-impact chronic pain, (3) greater reduction in substance use to manage pain, (4) greater reeducation in pain anxiety and depression, and (5) improved coping and self-efficacy. The second aim is to identify contextual factors that impact engagement, adoption, effectiveness, and implementation of nonopioid alternatives for LBP self-management. Understanding the external context and individual and team characteristics will help explain the results, provide important implementation perspectives, and inform translation.

## Methods

### Study Design

The exploration and preparation phases of the study were started in 2023, with the video training module creation, evaluation, modifications, and production completed in June 2024. A 2-arm pragmatic randomized controlled hybrid type II effectiveness and implementation study [42-44] will be conducted using mixed methods and a within-subject control period. The Standards for Reporting Implementation Studies (StaRI) standards checklist is included in Multimedia Appendix 1.

### Ethical Considerations

The study was approved by the University of Florida Institutional Review Board (IRB202300756) and registered as a clinical trial through ClinicalTrials.gov (NCT06153199). Participants will be compensated for their time. Workers will receive US $25 for the baseline data collection and US $50 for subsequent steps for a possible total of US $225, while supervisors or owners will receive US $50 for the 2 data collection sessions for a possible total of US $100.

Employers will provide permission to discuss the study with workers and to conduct the study in the workplace. After determining eligibility, research staff will describe the purpose of the study, study-related procedures, risks, and benefits, and participants will sign an informed consent if they agree to participate. We will ensure that participants understand that participation is voluntary and that they can withdraw from the study at any time without consequences. A Certificate of Confidentiality (42 USC §241(d)) will protect participant privacy related to potentially sensitive information about the use of pain medication and other substances. If individual workers are not eligible or do not want to participate, they will be able to view the educational videos with their teams. If participants who are randomly assigned to the intervention enhanced with multimodal support are not comfortable being videotaped, we will provide deidentified video clips of other workers with blurred faces performing tasks similar to the tasks they have identified as difficult due to pain.

### Recruitment

#### Recruitment Methods

We will recruit nursery and landscape workers in Florida through community partners and contacts from the Southeastern Coastal Center for Agricultural Health and Safety. We will use direct communication, email lists, websites, word-of-mouth referrals, and community meeting announcements to identify employers who are interested, followed by presenting the study to workers. We will recruit workers with a range of disability, pain impact, and persistence, anticipating that participants will be primarily male, with higher numbers of female participants in the nursery teams, and that approximately 50% will identify Spanish as their first language. Initial contact and permission will be through owners and supervisors to enroll nursery and landscape businesses and their employees.

#### Inclusion and Exclusion Criteria

Criteria for inclusion are (1) working full time (30 hours or more per week) in nursery or landscape businesses, (2) 18 years of age or older, (3) English or Spanish speaking, and (4) experiencing continuous or intermittent LBP over the past 3 months. We will exclude individuals who (1) report history of trauma, major spine surgery, or spinal nerve blocks in the past year; (2) are seeking disability or workmen's compensation, or (3) self-disclose pregnancy.

#### Sample Size Projections

A priori sample size was calculated using data from the pilot study comparing pain and disability measures pre and post–self-management PE interventions for 19 seafood workers [39]. For each participant and pain or disability outcome, averages of 4 baseline measurements and 2 postintervention measurements were used to calculate the difference in pre- to postintervention outcomes. Mean changes over a control period are assumed to have a mean 0 difference but share the same SD as the intervention period. Changes over the 2 periods for the same person are assumed to be independent. Data were simulated from a simple linear mixed model (LMM):

*Y_ijk_* = α*_i_* + β_1_*X_ijk_Z_ijk_* + β_2_(1 – *X_ijk_*)*Z_ijk_* + ε*_ijk_*

In this model equation, *Y_ijk_* is the outcome of observation period *k* of individual *j* in cluster *i*, *X_ijk_* indicates the intervention group (1: video + support, 0: video), *Z_ijk_* indicates the intervention period (1: intervention period, 0: baseline period), α*_i_* is the random intercept of cluster *i*, and ε*_ijk_* is the error term. The variance of α*_i_* was set as 5% of ε*_ijk_*, such that the intraclass correlation is close to 0.05. For each set of simulated data, a generalized estimation equation model was used to test the null hypothesis β_1_=0. We ran 1000 simulations to calculate the power for each of the different settings of the number of clusters and cluster sizes. Table 1 shows the power based on individual randomization. Fitting a LMM yielded comparable results. The planned enrollment of 102 participants (24 clusters) will provide adequate power for the primary outcomes, pain with most difficult work activities and total disability. An additional 20% enrollment for attrition results in a total anticipated sample of 30 clusters and 122 participants (teams of 3-5 participants) for the comparative effectiveness goals.

**Table 1 table1:** Statistical power (%) based on individual randomization for differentiating between the 2 implementation groups using preliminary data.

Number of clusters	Cluster size	Projected Sample size	Power (%) calculated using results from Dunleavy et al. [39].			
			Pain with most difficult work activities (mean –16.1, SD 18.8)^a^	Average pain (mean –5.2, SD 17.3)^a^	Total disability (mean –2.5, SD 3.5)^a^	Difficulty level with most problematic work activity (mean 9.0, SD 28.5)^a^
**20**						
	3	60	96.9	28.4	88.7	33.8
	5	100	99.8	43.9	98.3	49.5
	10	200	100	73.5	100	73.5
**25**						
	3	75	98.9	32.3	93.3	40.7
	5	125	100	48.6	99.4	57.5
	10	250	100	80	100	84
**30**						
	3	90	99.5	38.2	97.1	44.3
	5	150	100	56.3	99.8	64.4
	10	300	100	87.3	100	88.8

^a^Mean difference, SD from Dunleavy et al [39].

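### Table 1 takes its SDs from pilot changes between averaged measurements, but the trial analyses changes between single questionnaires, so the stated power is too high by an amount the article does not fix

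*Protocol article*

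**What the plan says.** The protocol article (Methods, Sample Size Projections) bases its power on a pilot "pre and post–self-management PE interventions for 19 seafood workers". The pilot change was formed from repeated measurements: "averages of 4 baseline measurements and 2 postintervention measurements were used to calculate the difference in pre- to postintervention outcomes". The Table 1 column headings carry the resulting values for the two primary outcomes: "Pain with most difficult work activities (mean –16.1, SD 18.8") and "Total disability (mean –2.5, SD 3.5").

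The same SD is applied to the control period: "Mean changes over a control period are assumed to have a mean 0 difference but share the same SD as the intervention period". Two further simulation assumptions are "Changes over the 2 periods for the same person are assumed to be independent" and a cluster variance chosen "such that the intraclass correlation is close to 0.05". The test is of β1=0, the coefficient for video + support in the intervention period. The article concludes that 102 participants in 24 clusters give adequate power for both primary outcomes.

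The trial's own schedule is in the Abstract: "Questionnaires will be administered at 3-month time points: baseline, pre- and postintervention, and at 3 and 6 months". The Timelines section likewise gives five measurement periods. Data Analysis, Aim 1, defines the outcome as the change over an observation period and uses the baseline, pre and post time points. The text describes no repetition or averaging within a time point.

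**The concern.** A mean of several scores is steadier than one score. The pilot change sets a mean of two against a mean of four; the trial's change sets one score against one score. If a worker's score varies from one occasion to the next for reasons unrelated to lasting change, the trial's change has the larger SD. Carrying 18.8 and 3.5 over unadjusted credits the trial with a precision that its measurement schedule does not provide. Because the same SD is used for the control period, both sides of the contrast are affected.

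At stake is the support for the claim about 102 participants, and mainly for total disability, the primary outcome with less margin.

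**Working it through.** **Inputs.** Effects and SDs from Table 1: pain 16.1 and 18.8, disability 2.5 and 3.5 (absolute values). N=102 and the β1=0 test are from Sample Size Projections. Allocation is 1:1 (Target Enrollment and Randomization). The significance level is not stated; two-sided 5% is assumed.

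**Reproducing Table 1.** β1 compares the N/2 intervention-period changes under video + support with the N control-period changes. The standard error is therefore SD × sqrt(2/N + 1/N) = SD × sqrt(3/N), and power = Φ(effect/SE − 1.96).

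| N | Pain, computed / stated | Disability, computed / stated |
|---|---|---|
| 60 | 96.9 / 96.9 | 89.1 / 88.7 |
| 90 | 99.7 / 99.5 | 97.5 / 97.1 |
| 100 | 99.9 / 99.8 | 98.5 / 98.3 |

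For N=60 and pain, for example: 18.8 × sqrt(3/60) = 4.20, 16.1/4.20 = 3.83, and Φ(1.87) = 96.9%. All cells for the two primary outcomes agree within 2 points; the two other columns differ by up to about 5.5 points in some cells. A GEE simulation with intraclass correlation 0.05 (300 runs per setting) gave 97.3% and 92.7% at 20 clusters of 3, and 100% and 98.7% at 20 clusters of 5. The pilot SDs therefore went in without inflation.

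**SD of a single-occasion change.** Let σ² be the occasion-noise variance of one score, independent between occasions, and T the part of the change variance that averaging does not reduce.

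- Pilot: variance = T + σ²(1/4 + 1/2) = T + 0.75σ²
- Trial: variance = T + σ²(1 + 1) = T + 2σ²

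With f = 0.75σ²/(T + 0.75σ²), the SD multiplier is sqrt(1 − f + f × 2/0.75). The article gives neither f nor a single-score SD, so f is taken over its whole range.

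**Power at N=102.** Here sqrt(3/102) = 0.1715.

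| f | Multiplier | SD pain / disability | Power pain / disability (%) |
|---|---|---|---|
| 0 | 1.00 | 18.8 / 3.50 | 99.9 / 98.6 |
| 0.25 | 1.19 | 22.4 / 4.17 | 98.7 / 93.8 |
| 0.5 | 1.35 | 25.5 / 4.74 | 95.8 / 86.8 |
| 0.75 | 1.50 | 28.2 / 5.25 | 91.5 / 79.3 |
| 1 | 1.63 | 30.7 / 5.72 | 86.4 / 72.3 |

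For disability at f=1, for example: 5.72 × 0.1715 = 0.98, 2.5/0.98 = 2.55, and Φ(0.59) = 72.3%.

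**Where disability crosses 80%.** This needs effect/SE = 1.96 + 0.84 = 2.80. At the stated SD the ratio is 2.5/(3.5 × 0.1715) = 4.165, so the multiplier is 4.165/2.80 = 1.49 and f is about 0.73.

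**The case against.** The strongest reply is that the conclusion which matters, adequate power at 102, mostly survives. Task pain keeps at least 86% in every scenario, and disability stays above 80% unless nearly three quarters of the pilot change variance is occasion noise. The 1.63 multiplier also requires that true change not vary between workers at all. This stands: the article's figures are too high, but they are not shown to be inadequate. A reader might infer from the 72% that the trial is underpowered; the documents do not support that, because nothing in them places f near 1.

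A reader might also take the between-arm comparison at the largest SD and note that the difference detectable with 80% power, 2.80 × 30.7 × sqrt(4/102) = 17.0, exceeds the whole pilot change of 16.1. That combines the worst-case SD with a different contrast (4/102 instead of 3/102). On the table's own contrast the figure is 2.80 × 30.7 × sqrt(3/102), about 14.8. Which contrast Table 1 should address is a separate question.

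Nor is there an arithmetic error in the primary columns of Table 1, which reproduce. The fault lies in the input.

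Could the trial average repeated questionnaires after all? Figure 1 is not shown, so the text has to serve. It names five time points, and the payments under Ethical Considerations fit five sessions: 25 + 4 × 50 = 225 dollars.

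Finally, Aim 1 already includes baseline pain or disability as covariates and an individual random intercept. These may recover some precision, but the article does not quantify this and the Table 1 model contains neither.

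**Conclusion.** The point holds as a mismatch between a planning input and the measurement schedule, and should be fixed. The direction is firm: if a single score carries any independent occasion noise, the SD behind every cell of Table 1 is understated and the power overstated. The size is open. At 102 participants, power lies between 86.4% and 99.9% for task pain and between 72.3% and 98.6% for disability, depending on a noise share that the article does not report.

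The range assumes two-sided 5%, equal and independent occasion noise, the pilot mean changes as true effects, and the article's own independence of the two period changes. That last assumption is itself open to question when one preintervention score ends one period and starts the next; this is a separate matter and is not counted here.

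**What to change.** From the pilot data, compute the SD of a single postintervention score minus a single baseline score. The four baseline and two postintervention measurements give 4 × 2 = 8 pairings per worker, which can be pooled, or the variance components can be estimated directly. Rerun the Table 1 simulation with that SD in both periods, restate power at 102 for both primary outcomes, and say in the text that the SD refers to single-occasion changes.

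The cost is a short re-analysis of existing data and revised power figures, with no change in enrolment.

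### Table 1 is presented as power to separate the two arms, but the simulated test compares the support arm with the control period, so power for the randomised comparison is overstated

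*Protocol article*

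**What the plan says.** The simulation model in Sample Size Projections has two effect terms. β1 multiplies X·Z and β2 multiplies (1 − X)·Z, where X is 1 for video + support and 0 for video, and Z is 1 for the intervention period and 0 for the baseline period. For each simulated data set, "a generalized estimation equation model was used to test the null hypothesis" β1 = 0. On the control period the section states: "Mean changes over a control period are assumed to have a mean 0 difference but share the same SD as the intervention period". It adds: "Changes over the 2 periods for the same person are assumed to be independent".

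The effect sizes are pre-to-post changes in a pilot of 19 seafood workers: −16.1 (SD 18.8) for pain with the most difficult work activities and −2.5 (SD 3.5) for total disability. No value is given for β2.

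Table 1 is captioned as power "for differentiating between the 2 implementation groups using preliminary data". The text then says that 102 participants give adequate power for these two primary outcomes. The next sentence inflates the number to 122 and ties it to the comparative effectiveness goals.

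Prior Work states: "The first aim is to determine if self-management videos combined with multimodal personalized support is more effective than self-management videos alone". The Conclusions of the Abstract hypothesise that "both self-management interventions will result in reductions in work task pain and disability".

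**The concern.** With Z = 0 as the reference, β1 is the support arm's change against the control period. The video-only arm enters only through β2, and the tested null does not involve β2. Rejecting β1 = 0 shows that workers given support improved more than they did during the control period. It does not show that support adds anything to video.

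The effect size adds to the problem. The pilot figures are whole uncontrolled pre-post changes, not increments over video alone. Using them for the arm contrast means taking β2 = 0, which conflicts with the stated expectation that both arms improve.

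The power of the randomised comparison is therefore not stated anywhere, while the reader is led to believe that it is close to 99%. A non-significant arm difference could then be taken as good evidence that support adds nothing, when the trial may have had little chance of detecting a realistic increment.

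**Working it through.** **Inputs.** Pilot means and SDs as above; 1:1 individual allocation (Target Enrollment and Randomization); N = 102 analysed, so 51 per arm; equal SD in both periods and independent changes within a person (Sample Size Projections). Two-sided alpha of 0.05 is my assumption, since none is stated. The cluster intercept is ignored in the closed forms and included in the simulation below.

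**Step 1. Reproduce Table 1 as a test of β1 = 0.** The support arm supplies N/2 intervention-period changes and all N workers supply control-period changes:

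SE = SD·√(1/(N/2) + 1/N) = SD·√(3/N), with power ≈ Φ(|effect|/SE − 1.96).

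At N = 60:
- task pain: SE = 18.8·√(3/60) = 4.204; 16.1/4.204 = 3.83; power 96.9%
- disability: SE = 3.5·√(3/60) = 0.783; 2.5/0.783 = 3.19; power 89.1%

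**Step 2. Compute the between-arm test in its most favourable plausible case, β2 = 0.** SE = SD·√(4/N). At N = 60 the SEs are 4.854 and 0.904, giving 91.3% and 79.0%.

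| N | Outcome | Table 1 | β1 = 0 | β1 = β2, with β2 = 0 |
|---|---|---|---|---|
| 60 | task pain | 96.9 | 96.9 | 91.3 |
| 60 | disability | 88.7 | 89.1 | 79.0 |
| 90 | task pain | 99.5 | 99.7 | 98.2 |
| 90 | disability | 97.1 | 97.5 | 92.3 |
| 100 | task pain | 99.8 | 99.9 | 99.0 |
| 100 | disability | 98.3 | 98.5 | 94.6 |

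Over all 36 cells, the β1 = 0 formula deviates from the table by 1.3 points on average. All 18 cells for the two primary outcomes are within 2 points. The largest gap, 5.5 points, is in the secondary columns. The between-arm formula deviates by 7.0 points on average and by up to 16.9.

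**Step 3. Repeat by simulation.** I used the stated model (cluster variance 5% of error variance, exchangeable GEE, 400 to 1000 runs per setting). At 20 clusters of 3, the test of β1 = 0 has 96.3% power for task pain and 88.6% for disability. For task pain, as β2 goes from 0 to half of β1 to equal to β1, this power stays at 96.3%, 97.5% and 95.8%. Power for β1 = β2 falls from 90.4% to 41.0% and then to 9.3%, which is the rejection rate when the arms do not differ. The tested hypothesis is insensitive to what video alone achieves.

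**Step 4. Between-arm power at N = 102.** SE is 18.8·√(4/102) = 3.723 for task pain and 3.5·√(4/102) = 0.693 for disability.

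| β2 as share of β1 | Difference, pain | Power | Difference, disability | Power |
|---|---|---|---|---|
| 0 | 16.1 | 99% | 2.50 | 95% |
| 25% | 12.1 | 90% | 1.88 | 77% |
| 50% | 8.05 | 58% | 1.25 | 44% |
| 75% | 4.03 | 19% | 0.63 | 15% |

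The β1 = 0 test at the same N has 99.9% and 98.6%.

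**Step 5. Detectable difference with 80% power.** 2.80·SE gives 10.4 points for task pain (10.4/16.1 = 65% of the pilot change) and 1.94 points for disability (1.94/2.5 = 78%).

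**The case against.** The strongest points on the other side are these.

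- **The tested hypothesis is not irrelevant.** The Objective in the Abstract lists the within-subject comparison first and the arm comparison second, and Data Analysis, Aim 1 keeps that order. Testing β1 = 0 answers part of that objective, for one arm. This is right, but Prior Work and the Discussion put support versus video alone first or as a coprimary aim, and the caption of Table 1 claims that comparison.
- **The analysis already compares the arms.** Data Analysis, Aim 1 lists video against video + support. The fault therefore lies in the power statement; type I error, randomisation and estimation are unaffected. This stands.
- **The low figures rest on an assumed β2.** If video alone has no effect, 102 analysed still gives 99% and 95%. This is correct, and it is why a range is shown. It is also the case that the protocol's own hypothesis rules out.
- **Baseline adjustment would help.** If covariates explained 25% of the variance (an assumption), power at the half-effect ratio would rise from 58% and 44% to about 70% and 55%, still below 80%.
- **Some β2 could fit the table.** At N = 60 the stated figures would match a between-arm test if video alone made workers slightly worse, by about 2.5 pain points or 0.37 disability points. For β2 between 0 and β1, no between-arm reading matches. The stated null of β1 = 0 fits without any such assumption.

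**Conclusion.** The concern holds. Table 1 gives the power of the support arm against a control period assumed to show no change, not power to tell the arms apart. The caption and the stated null contradict each other, and the tabulated figures side with the null.

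The size of the overstatement depends on β2, which the article does not give. At 102 analysed it is small if video alone is inert. It becomes serious if video alone achieves half or more of the support-arm effect: at half, power is 58% for task pain and 44% for disability. These figures assume two-sided 5% alpha, the pilot SDs, no covariate adjustment, and a support-arm effect equal to the full pilot change.

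**What to change.** 1. Recaption Table 1 as power for video + support against the within-subject control period.
2. Add power for H0: β1 − β2 = 0 from the same simulation, over a stated range of β2 such as 0, 25%, 50% and 75% of β1.
3. State the between-arm differences detectable with 80% power at 102 analysed (about 10.4 points for task pain and 1.94 for disability on the unadjusted calculation). Replace the general claim of adequate power with these figures.
4. Say in the sample-size section that β1 − β2 corresponds to the arm comparison already listed under Data Analysis, Aim 1.

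The cost is a re-run of existing code and revised wording, with less favourable stated power. Restating the power requires no extra participants. Reaching 80% power for the arm contrast when video alone gives half the effect is a different matter: 4·(2.80·SD/difference)², rounded up to equal arms, gives about 172 analysed for task pain and 248 for disability. If the sample stays at 102, the article should say plainly which increments the trial can and cannot detect.
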